**Introduction:**

Mitral valve replacement is a cardiac surgical procedure in which the diseased mitral valve is replaced by a mechanical or biological tissue valve.

Pulmonary physiology and mechanics are further disturbed after cardiothoracic surgery. Recovery from major surgery especially from open heart surgery is mainly affected by postoperative pulmonary complications (PPCs). The incidence of postoperative pulmonary complications is more frequent in upper abdominal and thoracic surgeries[1].

Cardiac Surgery may affect respiratory muscle function by a number of different mechanisms. For example, surgical incision of the chest wall affects the integrity of the respiratory muscles and provoke both alteration in demand and availability of energy for contraction of these muscles and thus directly affects their function leading to a reduction in the vital capacity (VC), tidal volume (VT), total lung capacity (TLC) and, thus, insufficient cough. Which in turn cause atelectasis in the basal lung segments and a decrease in functional capacity (FRC)[2]**.**

In any major surgery, like, thoracic, or abdominal surgery, weighing benefits and risks is crucial for decision. With regard to risks arising from surgery, the prevention of postoperative pulmonary complications (PPC) is relevant, as they are strongly associated with increased morbidity and mortality, and decreased quality of life. The most common PPC are atelectasis, pneumonia, bronchospasm, embolus, acute respiratory distress syndrome, respiratory failure with prolonged mechanical ventilation, pleural disorders and diaphragmatic and/or chest wall dysfunction [1,3–5]. PPC seem to play an important role in length of hospital stay (LOS) and treatment costs [1,2,6].

Inspiratory muscle training (IMT) might be an important strategy to reduce PPC and LOS after major surgery, especially those involving respiratory muscle and chest wall damage. Aiming at elucidating the potential benefits of IMT on PPC and LOS, several meta-analyses have been conducted, but all analysing only preoperative IMT[3–6].

In their systematic review, Kendal et al.,[1] reported that there is paucity of the available literature investigating the effectiveness of postoperative IMT and its proper dose prescription [ie, starting load, maximal achieved load, Load increment, intervention duration, frequency, duration of sessions and the degree of supervision], which makes it difficult to ascertain the effectiveness and the preventive ability of IMT in reducing the risk of developing PPC.

Few studies had investigated the effectiveness of postoperative IMT with different methodologies, small sample size, different protocols, different durations of intervention with some supporting one week of intervention[7], while others investigated the effect of two weeks of interventions[8]. Different methodologies and unclear IMT parameters makes it difficult to compare between previous studies and consequently difficult to make clinical recommendation for using the postoperative IMT.

Pulmonary function values measured by computerized spirometry is simple and safe investigation routinely used in clinical practice for the diagnosis and evaluation of a variety of pulmonary diseases. The most important of these tests include spirometry. Pulmonary function values are based on sex, heights, weight and age. When the patient performs the test, actual results (observed) will be compared with the predicted values expected of a person of gender, height, and age to see if he falls within the "normal" range, or has a restrictive or obstructive component based on the results of the tests [9].

The Six minute walk test (6MWT) is used to measure cardiovascular endurance and functional capacity following abdominal and cardiothoracic surgery. Spirometry is a gold standard outcome measure, used to assess pulmonary function[10]. Spirometry and 6MWT are excellent tests for assessing pulmonary function and functional capacity before and after open abdominal and cardiothoracic surgery[11]

**Statement of the problem:**

Does postoperative high load long duraion inspiratory muscle training (IMT) affect pulmonary function and functional capacity after Mitral valve replacement surgery?

**Purpose of the study:**

The purpose of the study was to investigate the effect of the postoperative high load long duration inspiratory muscle training on pulmonary function and functional capacity after mitral valve replacement.

**Significance of the study:**

Reductions in oxygenation, pulmonary function, and respiratory muscle strength, as well as radiological changes such as atelectasis have been cited as common alterations in postoperative cardiac surgery. The reduction of Respiratory Muscle Strength (RMS), resulting from direct or indirect lesion of respiratory muscles during surgery and the secondary diaphragmatic dysfunction due to phrenic nerve lesion, has also been related to reduced pulmonary function tests, worsened gas exchange, and increase in the rate of pulmonary complications [12]**.**

It was reported that high load pre-operative IMT was related to reduction in PPC[1,13] however, to the best of our knowledge, there is no study had investigated the effectiveness of using different doses of IMT postoperatively. Since, the benefits of IMT was related to the prescribed dose[1], this study was designed to investigate the effect of high load long duration (8 weeks) supervised IMT on pulmonary function, and functional capacity after mitral valve replacement. That will investigate the effectiveness of IMT dose (High load , long duration, supervised training) on pulmonary function and functional capacity. Furthermore, the study design (prospective randomized controlled trial with follow up) will help clinicians and researchers to track the progress and changes in pulmonary functions, inspiratory muscle strength and functional capacity over a long period of time after Mitral valve surgery. Furthermore, the follow up assessment will provide an evidence about the long term effect of high load IMT

**Hypotheses:**

It was hypothesized that there will be an effect of postoperative IMT on pulmonary function after mitral valve replacement

**REVIEW OF THE RELATED LITERATURE**

Mitral valve disease patients may exhibit reductions in lung volumes due to inspiratory muscle weakness in cases of pulmonary vascular congestion. The inspiratory muscles are compromised due to poor nutritional status that lead to decreased muscle mass and strength, increased work of breathing, in cases of long-standing mitral valve disease [14,15].

Pulmonary hypertension develops in these patients also, as a result of combination of transmission of raised left atrial pressure, pulmonary arteriolar vasoconstriction and obliterative changes in the pulmonary circulation [16].

The incidence of postoperative pulmonary complications is more common in upper abdominal and cardiothoracic surgeries and may include pleural effusion, atelectasis, pneumothorax, bronchospasm, respiratory infection, respiratory failure, pneumonia, acute respiratory distress syndrome (ARDS), and pulmonary embolism [17].

The cardiac surgeries predispose to abnormal changes in respiratory mechanics, lung volumes and gas exchange, leading to development of postoperative respiratory changes. These changes are due to various causes [such as the condition of the heart and lung preoperatively, the degree of sedation, intensity of surgical manipulation and the number of pleural drains] which leads to development of abnormal respiratory mechanics in the immediate postoperative period [18,19].

Mitral valve surgery causes insufficient diaphragmatic breathing post operatively which contributes significantly to development of postoperative pulmonary complications. Consequently, there are consistent reductions in pulmonary volumes and flows, alveolar collapse, reduction of sputum clearance ability, increase of respiratory work and diminution of mechanical efficiency of the respiratory muscles [3].

Inspiratory muscle training is one of the procedures followed to promote better efficacy in airway clearance, improving inspiratory pressure and prevent fatigue of the respiratory muscles [20], which aims to improve functional capacity, respiratory muscle strength and reduce imminent risks of developing post-operative complications in patients undergoing cardiovascular surgery [21].

In phase I of Cardiac Rehabilitation various physiotherapy techniques are routinely used such as diaphragmatic breathing exercises, effective cough, chest wall percussion and vibration, continuous Positive Airway Pressure (CPAP) may prevent further deterioration in pulmonary function and reduce the incidence of Post-operative pulmonary complications[17,22,23]. Unfortunately, There is a controversy about the efficacy of these postoperative procedures in decreasing the incidence of Post-operative pulmonary complications and improving pulmonary flows and volumes [4].

Inspiratory muscle training (IMT) is a therapeutic tool and one component of pulmonary rehabilitation which improves respiratory muscle strength, reduce the severity of dyspnea, improve the exercise tolerance and improve pulmonary flows and volumes after cardiothoracic surgery [4,24].

**MATERIALS AND METHODS**

**Design of the study:**

Randomized controlled trial

**Sample size calculation:**

A Priori sample size calculation was performed using G*Power 3.1.9.4 software (Heinrich-Heine-Universität Düsseldorf, Düsseldorf, Germany; <http://www.gpower.hhu.de/>). Alpha level will be set at α = 0.05, the statistical power was set at 90%; confidence level of 95% and effect size of 0.7 for FVC obtained from our previous pilot study, the sample size was calculated as 44 participants per group (total number of 88). Anticipating an attrition rate of 10-15%, so fifty participants will be recruited in each group (total sample size n=100).

**Outcome measures:**

The primary outcome measures will be the pulmonary function measures and the inspiratory muscle strength obtained by measuring maximal inspiratory pressure (MIP).The secondary outcome measure will be the functional capacity evaluated by 6-minute walk test (6MWT).

**Participants:**

All participants will be patients aged 25-50 years recruited from the waiting list for elective Mitral valve replacement (MVRS) at South Valley university hospital.

The inclusion criteria are:

1. patients undergoing elective MVRS
2. participants aged 25-50 years
3. normal body mass index (BMI)
4. post-operative medically and clinically stable
5. Able to walk independently without any assistive devices.

The exclusion criteria are:

1) Obesity (BMI ˃ 30kg/m^2^)

2) Postoperative hemodynamic complications such as lung congestion or myocardial infarction

3) History of pulmonary diseases or infection such as chronic obstructive pulmonary diseases (COPD) or tuberculosis

4) Smokers

5) Post-operative renal failure

6) Cardiac arrhythmia or unstable angina

7) Uncontrolled hypertension

8) Post-operative hemodynamic instability

9) Post-operative prolonged ventilation [more than 24 hours]

10) Neurological/ musculoskeletal disorders that could affect functional capacity or pulmonary function such as(parkinsonism, ankylosing spondylitis, scoliosis, ….etc)

11) History of previous cardiothoracic surgery.

**Study Setting:**

South Valley University Hospital; Qena; Egypt

Anticipated trial start date: Jun 2019

Anticipated last follow up date: January 2020

**Randomization, allocation concealment:**

The patients will be randomly selected using simple randomization method. After surgery, random allocation of patients will be performed through sequentially numbered sealed opaque envelops. The sequentially numbered envelops will be arranged and sealed by an independent statistician who will not be involved in the study. These envelops will be given to the allocator. The allocator will be blinded to the study objectives and will not participate either in the intervention or the assessment procedures. The allocation ratio will be 1:1. Each envelop will be opened only in front of the patient to be assigned. Fifty participants were randomly allocated to each of the experimental group (n=50) and control group (n=50).

**Procedures:**

The patients will be admitted to the hospital one day before surgery. This is a routine procedure followed for any patient undergoing cardiothoracic surgery for laboratory investigation, general check-up, pulmonary function testing and pre-operative physiotherapy education. This preoperative education session consisted of instructions about surgery and the importance of physiotherapy program to avoid PPC, training for breathing exercise [ Diaphragmatic breathing, segmental breathing], coughing and huffing techniques, ankle pump exercise, lower limb active range of motion (ROM) exercise as well as training for mobility and transfer activities. The purpose of this preoperative education is to help the patients to do these exercises much easier in the postoperative period as they become aware about these exercises in advance.

Assessment of Pulmonary function, MIP will be performed preoperatively (one day before surgery) as a baseline assessment, on the first day in the inpatient ward, on the day of discharge from hospital, by the end of the first postoperative month, by the end of 8^th^ postoperative week and after 6 months from date of surgery (Follow up). Pulmonary function measurements will be performed at rest using a computer-based spirometry system (Eric Jaeger- Germany). The measurement will be done from a relaxed sitting on a height adjustable chair with arm support (to prevent falling sideways just in case if syncope occur), with feet supported on the floor, keeping spine erect with shoulders slightly back and using disposable nasal clip and mouth piece for each patient which must be disposed at the end of testing session.

The studied spirometry parameters in this study are the forced vital capacity (FVC), forced expiratory volume in one second (FEV_1_), and FEV_1_/FVC ratio. The highest value from at least three technically acceptable spirometric maneuvers will be recorded. Pulmonary function measurements will be performed by an independent examiner who will be blinded to the study objectives, group allocations and intervention. This examiner will not participate in the intervention procedures.

Measurement of MIP will be performed using a portable electronic respiratory mouth pressure meter device (Micro RPM, Micro Medical Ltd, Kent, UK). The measurements will be performed from comfortable sitting position with a nose clip. The MIP is measured by deep inspiration through the mouthpiece only from the residual volume after maximal expiration. Leaning forward will not be allowed during testing as it can overestimate the measurement value.

To ensure reproducibility, Testing will be repeated with 1-min interval for three technically satisfactory trials with less than 5% difference, and the highest value will be used to define MIP expressed in centimeters of water (cmH_2_O).

Functional capacity will be examined using a six minute walk test (6-MWT). The participants will be instructed to walk as far as possible without running in six minutes in an enclosed 30-m long hospital corridor. Standardized encouragement will be given every 30 sec, the maximum distance covered at the end of the test will be recorded. For safety, Heart rate (HR), respiratory rate, blood pressure (ABP), and oxygen saturation will be measured before, during and after the test. The test will terminated, if the HR and/or ABP increases by ≥20% of baseline values. The test will be performed twice separated by a recovery period of 15 minutes, and then the mean of the two trials will be recorded.

The test will be performed on the baseline assessment (one day before surgery), on discharge from hospital, 4 weeks from surgery, after 8 weeks from surgery and after 6 months from surgery (Follow up).

Both groups will receive the routine postoperative physiotherapy protocol [Diaphragmatic and segmental breathing exercise, coughing techniques, active cycles of breathing techniques, and active exercise for upper and lower limbs, early ambulation program]. This traditional physiotherapy program will be performed daily till discharge from the hospital.

In addition to the traditional physiotherapy program, the experimental group will receive IMT using a pressure threshold loading device (Threshold Inspiratory Muscle Training, Respironics, Pittsburg, PA, USA). This device allows variable loading at a detectable intensity by providing air flow-independent resistance to inspiration using a spring-loaded one way valve. Changing spring length results in the same change in the valve opening pressure. This spring-loaded valve opens only when the inspiratory pressure generated by the patients exceeds the spring tension.

At the beginning of the postoperative intervention, the patients started training with 40% MIP recorded pre-operatively. MIP will be measured weekly to adjust the training intensity. The intensity will be increased incrementally by 5%-10% according to patient tolerance each week targeting 80% of the preoperatively determined MIP by the end of 8^th^ week after surgery. To ensure safety of the training, HR, blood pressure, oxygen saturation and respiratory rate will be monitored during training sessions.

Training will be performed and supervised by a single physiotherapist. This physiotherapist will be blinded to the group allocation and the study objectives. The training load was continuously monitored to ensure achievement of the target MIP. The patients will receive postoperative IMT for 20-30 min/session in the form of six sets, each set consisted of five deep breaths against the IMT device, with a short interval of 1-2minute rest between sets. Training will be performed on daily basis, twice per day till discharge from hospital. Training will be performed from comfortable sitting position using nose clip in every training session and patients were instructed to inspire through a mouth piece at the desirable training load.

On the day of discharge from hospital, all measurements will be repeated for all patients (pulmonary function measurements, maximal inspiratory pressure, and functional capacity). After discharge from the hospital, the patients will be instructed to visit the outpatient cardiopulmonary rehabilitation unit for continuing intervention program under supervision and for ensuring that patients will receive the proper training load. Training will be performed four times per week till the eighth postoperative week.

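### The single 'highest value' rule for spirometry, read as written, records FEV1/FVC as a per-blow maximum, which shifts the ratio upward by an uncontrolled amount (minor)

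*Protocol*

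**What the plan says.** In the protocol's Procedures section the spirometry outcomes are introduced thus: "The studied spirometry parameters in this study are the forced vital capacity (FVC), forced expiratory volume in one second (FEV_1_), and FEV_1_/FVC ratio". The next sentence is the only recording rule for them: "The highest value from at least three technically acceptable spirometric maneuvers will be recorded". It does not exempt the ratio, say how the ratio is derived, or cap the number of manoeuvres.

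The Outcome measures section gives these parameters primary status: "The primary outcome measures will be the pulmonary function measures and the inspiratory muscle strength". FEV1/FVC is therefore one of four primary measures, with FVC, FEV1 and MIP.

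Two other statements bear on the point. For MIP, the Procedures section sets a repeatability limit ("three technically satisfactory trials with less than 5% difference"); it states none for spirometry. The spirometry examiner is "blinded to the study objectives, group allocations and intervention".

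**The concern.** For FVC and FEV1 the largest value is the best effort, so taking the highest is sensible. A ratio has no such property. Its per-blow maximum comes from a blow with a relatively short FVC, a relatively high FEV1, or both. Taking the maximum of a noisy quantity also pushes the recorded value above its true level, and further up as blows are added or become more variable.

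Two things are at stake. First, the three recorded spirometry values will generally not agree with each other: the ratio will exceed the quotient of the two volumes. Second, the size of the excess depends on the number and consistency of blows, which the protocol does not control. Spirometry is done six times, from the day before surgery through the first ward day to six months. If blow consistency changes over that course, the recorded ratio moves over time without any change in lung function, and the repeated-measures ANOVA would show this as a time effect. If consistency or number of blows also differs by arm, it would appear in the group comparison.

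**Working it through.** **The plan's own figure.** The protocol states no figure for this bias. Its sample size rests on an "effect size of 0.7 for FVC obtained from our previous pilot study". With d = 0.7, two-sided alpha 0.05 and a two-sample t test, power is 0.894 at 43 per group and 0.901 at 44, so the stated 44 per group reproduces. It is based on FVC and is untouched by how the ratio is recorded.

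**Direction, without assumptions.** Let E and V be FEV1 and FVC in each blow of a session, and let j be the blow with the highest E. Then

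max(E/V) ≥ E_j/V_j = max(E)/V_j ≥ max(E)/max(V),

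because V_j cannot exceed max(V). So in every session the highest per-blow ratio is at least recorded FEV1 over recorded FVC.

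**Size, under assumptions.** The documents give no blow-to-blow variation. Assumed: true ratio 0.80; CVs of 2-5% for FVC and FEV1; correlation r between them of 0 to 0.8; 3, 5 or 8 blows. Each scenario was simulated with 200,000 sessions. Shifts are percentage points from 0.80.

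| CV FVC | CV FEV1 | r | Highest ratio: 3 / 5 / 8 blows | Highest FEV1 over highest FVC: 3 / 5 / 8 blows | Chosen blow has smallest FVC (3 blows) |
|---|---|---|---|---|---|
| 2% | 2% | 0.5 | +1.38 / +1.89 / +2.31 | +0.01 / +0.01 / +0.01 | 54% |
| 3% | 3% | 0.5 | +2.08 / +2.86 / +3.51 | +0.03 / +0.02 / +0.01 | 54% |
| 3% | 3% | 0 | +2.97 / +4.08 / +5.01 | +0.04 / +0.02 / +0.02 | 65% |
| 3% | 3% | 0.8 | +1.30 / +1.79 / +2.20 | +0.02 / +0.01 / +0.01 | 46% |
| 5% | 5% | 0.5 | +3.52 / +4.85 / +5.97 | +0.06 / +0.04 / +0.04 | 54% |
| 5% | 3% | 0.5 | +3.15 / +4.34 / +5.35 | -1.23 / -1.71 / -2.07 | 71% |
| 5% | 2% | 0.5 | +3.18 / +4.37 / +5.40 | -1.87 / -2.57 / -3.13 | 81% |
| 3% | 5% | 0.5 | +2.96 / +4.08 / +4.99 | +1.33 / +1.81 / +2.19 | 38% |

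**Hand check of one cell.** The relative SD of the per-blow ratio is about √(CV_V² + CV_E² − 2r·CV_V·CV_E). At 3%, 3%, r = 0.5 this is √(0.0009 + 0.0009 − 0.0009) = 0.03. The expected maximum of three standard normal values is 3/(2√π) = 0.846. The shift is then about 0.80 × 0.03 × 0.846 = 0.0203, or 2.0 points, against 2.08 simulated.

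**Effect on the treatment contrast.**
- Same number and spread of blows in both arms: difference about 0.
- CV 5% in one arm and 3% in the other, 3 blows: 1.4 points at r = 0.5. With correlated lognormal errors it is 0.842 − 0.825 = 0.017 at r = 0.3 and 0.827 − 0.816 = 0.011 at r = 0.7, so about 1.1 to 1.7 points. The more even arm is recorded lower.
- CV 3% in both arms, 5 blows against 3: 0.8 points.
- CV 5% with 5 blows against CV 3% with 3 blows: 2.8 points.

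**The case against.** The strongest reply is that the sentence never says that the highest FEV1/FVC is recorded. It could mean highest FVC and highest FEV1, with the ratio derived from them, and the derivation of a computed variable can be left to an analysis plan that is not shown. This stands in part: that reading is possible. But it must be inferred, because the sentence directly follows a list that includes the ratio and exempts nothing. If it is what was meant, the same correction makes it explicit.

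Several stronger conclusions are tempting and are not supported.

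- **That the rule picks the blow with the shortest FVC.** It only favours such blows. With three blows and equal CVs the chosen blow has the smallest FVC in about 48-58% of sessions for r of 0.7 to 0.3; a high FEV1 often drives the maximum. The requirement for technical acceptability also limits poor blows.
- **That the treatment effect on the ratio is biased.** The rule is the same in both arms and the examiner is blinded. Blinding does not stop a difference that comes from patients' own performance, but nothing in the protocol shows that blow number or spread differs by arm. If trained patients blow more evenly, the rule records them lower than controls.
- **That the whole gap between the maximum ratio and the quotient is bias.** At CVs of 5% (FVC) and 3% (FEV1), r = 0.3 and 3 blows, the gap is 0.835 − 0.787 = 0.048. Only 0.835 − 0.800 = 0.035 is upward shift; the remaining 0.013 is downward error in the quotient.
- **That the shift can be judged against the planned effect of 0.7.** That figure is for FVC. No effect is planned for the ratio, and the documents give no SD for it.

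**Conclusion.** The concern holds as a minor point. On its plain reading the protocol records a primary measure, FEV1/FVC, as a per-blow maximum. The direction of the discrepancy from the recorded volumes is certain. Its size is not: the range of 1.3 to 6.0 points above a true 0.80 comes from the eight combinations of assumed CVs and correlations in the table, and would be smaller or larger outside them.

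What is affected for certain is the level of the ratio. Distortion of change over time or of the group contrast is conditional on differences in blow number or consistency by visit or by arm, which the documents neither show nor rule out. Under an assumed 5% against 3% CV with three blows, the false difference would be about 1.1 to 1.7 points.

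**What to change.** In the Procedures section, limit the highest-value rule to FVC and FEV1. Add that FEV1/FVC is calculated as the recorded highest FEV1 divided by the recorded highest FVC, is never itself selected as a maximum, and is derived this way at all six assessments.

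The cost is one sentence. Both volumes are already recorded, so no new measurement is needed. There is a small downside: the quotient is not exactly unbiased when the two CVs differ. In the scenarios above it is off by -1.2 to -3.1 points when FVC varies more and by +1.3 to +2.2 points when FEV1 varies more. It is essentially unbiased when the CVs are equal, and it always agrees with the two recorded volumes.

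### The physiotherapist who delivers IMT cannot be blinded to allocation, and blinded assessment is stated for spirometry but not for MIP (primary) or 6MWT (secondary)

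*Protocol*

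**What the plan says.** All the relevant statements on treatment and testing are in the Protocol, Procedures.

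- **Treatment.** "Both groups will receive the routine postoperative physiotherapy protocol", and then: "In addition to the traditional physiotherapy program, the experimental group will receive IMT using a pressure threshold loading device". No sham or unloaded device is described for controls.
- **Who trains.** "Training will be performed and supervised by a single physiotherapist", followed directly by "This physiotherapist will be blinded to the group allocation and the study objectives".
- **Blinded assessment.** "Pulmonary function measurements will be performed by an independent examiner who will be blinded to the study objectives, group allocations and intervention". The spirometry parameters listed are FVC, FEV1 and their ratio. This examiner takes no part in the intervention.
- **MIP and 6MWT.** The MIP paragraph opens "Measurement of MIP will be performed using a portable electronic respiratory mouth pressure meter device" and describes posture and repeat trials. The 6MWT paragraph describes the corridor, encouragement at fixed intervals and two trials. Neither paragraph says who does the testing or whether that person is blinded.
- **Extra MIP testing.** Within the IMT description only: "MIP will be measured weekly to adjust the training intensity".

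Outcome measures makes pulmonary function and MIP primary, named as two things, and 6MWT secondary. Ethical consideration has every participant told the study objectives.

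**The concern.** Three separate issues meet here.

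First, a person who puts a threshold device in a patient's hands and sets its load knows that this patient is in the IMT group. Blinding to the study objectives is conceivable; blinding to allocation is not. If the sentence were carried into the report, it would be an untrue blinding claim.

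Second, MIP and 6MWT are effort-dependent, and the tester instructs or encourages the patient. Patients know the objectives and, without a sham, know their treatment. A blinded tester is the main protection left, and the plan states that protection for spirometry alone.

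Third, MIP is both a primary outcome and the reading used to set the training load. If the weekly tests are done only in patients who have a load to set, the IMT arm performs the outcome manoeuvre more often than the control arm. Any gain from familiarity with the test would then look like a gain in strength, and the planned group-by-time ANOVA could not separate the two.

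**Working it through.** **1. Can the treating physiotherapist be blinded to allocation?** One person performs and supervises the training; only one arm trains; no sham exists. Delivering the training therefore reveals the allocation. The statement contradicts the design.

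**2. How far does the stated assessor blinding reach?**

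- Procedures assigns the blinded examiner to pulmonary function measurements and lists three spirometric parameters. MIP is not among them.
- Outcome measures lists pulmonary function and MIP as separate primary measures.
- The discharge-day sentence in Procedures lists three things: pulmonary function, MIP and functional capacity.
- MIP and 6MWT have their own paragraphs, and MIP its own device; neither paragraph names an assessor.

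On its wording, the blinding statement covers spirometry. For MIP and 6MWT the Protocol is silent.

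**3. MIP test occasions up to week 8.**

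Scheduled in both arms (Procedures): preoperative, first ward day, discharge, end of month 1, end of week 8 = 5. A sixth follows at 6 months.

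Weekly tests over 8 weeks in the IMT arm: up to 8.

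| Overlap of weekly with scheduled tests | IMT arm | Control arm | Ratio |
|---|---|---|---|
| None | 5 + 8 = 13 | 5 | 13/5 = 2.6 |
| Month 1 and week 8 coincide | 13 − 2 = 11 | 5 | 11/5 = 2.2 |
| Discharge coincides as well | 13 − 3 = 10 | 5 | 10/5 = 2.0 |

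So 2.6 is a ceiling and 2.0 to 2.2 is the likelier range. With the 6-month test included, the same three rows give 14/6 = 2.3, 12/6 = 2.0 and 11/6 = 1.8.

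**4. What a bias of a given size would do (illustration under assumption).** The documents give no size for a practice or assessor effect, so a range is shown. Take a single two-sided 5% t-test on MIP with no true effect and a spurious advantage of b standard deviations in the IMT arm. The rejection probability comes from the noncentral t distribution with 2n − 2 degrees of freedom and noncentrality b × √(n/2). For example, b = 0.3 and n = 50 gives 0.3 × 5 = 1.5.

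The same formula reproduces the Protocol's own sample size: effect size 0.7, two-sided 5% (sidedness is not stated) and n = 44 per group give power 0.901 against the stated 90%.

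| Spurious advantage b (SD) | n = 44 per group | n = 50 per group |
|---|---|---|
| 0.1 | 0.08 | 0.08 |
| 0.2 | 0.15 | 0.17 |
| 0.3 | 0.29 | 0.32 |
| 0.5 | 0.64 | 0.70 |

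This simplifies the planned repeated-measures ANOVA and serves only to show sensitivity. It does not estimate the bias in this trial.

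**The case against.** The strongest reply is that the false sentence by itself biases nothing. The physiotherapist is nowhere named as an outcome assessor, and spirometry has a separate blinded examiner. That is right. A reader might infer that the treating physiotherapist collects the MIP outcome data, or that MIP and 6MWT are tested unblinded. The documents say neither; they name no tester, and silence is not a statement of unblinding.

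It can also be argued that the Protocol uses its terms loosely. Procedures introduces pulmonary function and MIP together, and Statistical analysis speaks only of lung functions and functional capacity, so MIP might be meant to fall under pulmonary function. That leaves some ambiguity for MIP, but two other places list it separately, and no reading brings 6MWT under the blinded examiner.

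The test procedures also limit bias. MIP needs three satisfactory trials within 5% of each other, in a fixed posture with a nose clip. The 6MWT uses standardised encouragement and the mean of two trials. These controls help but do not replace a blinded tester.

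On the weekly tests, three limits stand:

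- The text does not say that controls are not tested weekly. That is an inference from where the sentence stands and what the test is for.
- A ratio of test occasions is not a size of bias.
- A reader might extend the practice argument to 6MWT. The documents do not support this: its schedule is the same in both arms and the weekly test is MIP only.

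Finally, a reader might conclude that MIP should lose its primary status. That does not follow. It directly measures the muscle function being trained, and a blinded examiner deals with the detection problem.

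**Conclusion.** The point holds, with different strength in its three parts.

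- **Certain from the text:** the treating physiotherapist cannot be blinded to allocation under this design, so the statement is wrong as written.
- **Firm on the wording:** blinded assessment is stated only for pulmonary function measurements. A primary and the secondary outcome, both effort-dependent, have no stated protection against detection bias. The gap is one of unstated protection, not proven unblinding.
- **By inference:** up to week 8 the IMT arm has roughly 2.0 and at most 2.6 times as many MIP test occasions (10 to 13 against 5), assuming that the weekly load-setting tests are confined to that arm and run for 8 weeks. A practice effect on MIP is possible and its size is unknown.

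Nothing here touches the spirometric outcomes, whose blinded examiner is stated. The changes should be made, but the point does not invalidate the trial.

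**What to change.** 1. Delete the claim that the treating physiotherapist is blinded to group allocation.
2. Assign MIP and 6MWT, at every scheduled assessment, to the independent blinded examiner who already performs spirometry, and ask patients not to reveal their group to that examiner.
3. State that only this examiner's scheduled MIP readings are outcome data and that the weekly load-setting readings are excluded.
4. Report the unequal number of MIP test occasions as a limitation when interpreting MIP. Equal practice manoeuvres before scheduled visits would not remove it, because they do not equalise cumulative exposure.

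**Cost.** No new role is needed, since someone must run these tests anyway, but the time shifts to one examiner and is not trivial. From the Protocol's own procedure, one 6MWT session takes 6 + 15 + 6 = 27 minutes. At 5 time points for 100 patients that is 27 × 500 = 13,500 minutes, or 225 hours before attrition, plus the MIP tests. The other cost is a less favourable, but accurate, blinding statement.
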